# Robot-assisted single-site compared with laparoscopic single-incision cholecystectomy for benign gallbladder disease: protocol for a randomized controlled trial

**DOI:** 10.1186/s12893-017-0206-1

**Published:** 2017-02-09

**Keywords:** Single Site, Single incision, Cholecystectomy, Robot-assisted laparoscopy, da Vinci, Surgeon’s Comfort, Stress load

## Abstract

**Background:**

Recent advances in robotic technology suggest that the utilization of the da Vinci Single-Site™ platform for cholecystectomy is safe, feasible and results in a shorter learning curve compared to conventional single-incision laparoscopic cholecystectomy. Moreover, the robot-assisted technology has been shown to reduce the surgeon’s stress load compared to standard single-incision laparoscopy in an experimental setup, suggesting an important advantage of the da Vinci platform. However, the above-mentioned observations are based solely on case series, case reports and experimental data, as high-quality clinical trials to demonstrate the benefits of the da Vinci Single-Site™ cholecystectomy have not been performed to date.

**Methods:**

This study addresses the question whether robot-assisted Single-Site™ cholecystectomy provides significant benefits over single-incision laparoscopic cholecystectomy in terms of surgeon’s stress load, while matching the standards of the conventional single-incision approach with regard to peri- and postoperative outcomes. It is designed as a single centre, single-blinded randomized controlled trial, which compares both surgical approaches with the primary endpoint surgeon’s physical and mental stress load at the time of surgery. In addition, the study aims to assess secondary endpoints such as operating time, conversion rates, additional trocar placement, intra-operative blood loss, length of hospital stay, costs of procedure, health-related quality of life, cosmesis and complications. Patients as well as ward staff are blinded until the 1^st^ postoperative year. Sample size calculation based on the results of a previously published experimental setup utilizing an estimated effect size of surgeon’s comfort of 0.8 (power of 0.8, alpha-error level of 0.05, error margin of 10–15%) resulted in a number of 30 randomized patients per arm.

**Discussion:**

The study is the first randomized controlled trial that compares the da Vinci Single Site™ platform to conventional laparoscopic approaches in cholecystectomy, one of the most frequently performed operations in general surgery.

**Trial registration:**

This trial is registered at clinicaltrials.gov (trial number: NCT02485392). Registered February 19, 2015.

## Background

Recent technological advances in both standard and robotic laparoscopic technology suggest that the surgical removal of the gallbladder can be done safely and effectively using the single port technique through one small periumbilical incision, which results in less scarring and possibly better cosmetic and clinical outcomes for the patient [1–6]. Despite beneficial patient-related results of laparoscopic single port cholecystectomy compared to the multiport laparoscopic operation, surgeons do not feel comfortable with the single port technology [6]. Hereby, the Da Vinci Single-Site™ technology provides several putative advantages over standard laparoscopic single-incision approaches such as the utilization of ergonomic, curved robot-assisted devices that preserve triangulation within the operative field, the reassignment of the crossing instruments to the opposite side, motion scaling and a stable 3D view of the operating field. These interesting features are thought to reduce eye strain, improve the ergonomic outcomes for surgeons and minimize both the mental and the physical workload associated with single-incision laparoscopy. Thus they possibly improve both surgical performance and work satisfaction, as well as eventually impact beneficially on patient well-being and outcome [3, 7].

Indeed, preliminary evidence from case reports and case–control studies suggests that the utilization of the da Vinci Single-Site™ technology for cholecystectomy is safe, feasible and results in a shorter learning curve compared to conventional single-incision laparoscopic cholecystectomy [1–4]. Hereby, some of the best evidence regarding robot-assisted single-site cholecystectomy comes from a study by Pietrabissa [3]. They conducted a multicenter, prospective, observational study, which included a total of over 100 robotic procedures. In this cohort, the authors reported no major intraoperative complications and only two of the cases were converted to an open procedure due to inflammation. All of the participating surgeons that had previous experience with single-incision laparoscopy cholecystectomy agreed that the robotic approach is easier than the single-incision laparoscopic technique.

Additional evidence for the benefits of the Da Vinci platform comes from a study by Schatte and colleagues [7]. Hereby, in a simulated experimental setup, the computer-aided technique significantly associated with cognitive and physical stress reduction. It has been therefore suggested that the utilization of the da Vinci robot system may provide several advantages to professionals who complain of fatigue and discomfort when conducting modern surgical procedures, such as single-incision laparoscopy. Indeed, surgeons are a group of health care professionals who are at risk of developing work-related musculoskeletal disorders because of many physical and psychosocial risk factors [8, 9]. Moreover, increases in technological complexity and equipment that is sometimes poorly adapted to new techniques have led surgeons to increasingly complain of fatigue when conducting modern surgical procedures [8, 10–13]. Importantly, it has been shown that a surgeon’s degree of burnout resulting from such fatigue and discomfort experienced at his or her workplace is strongly correlated with major medical errors, which in turn carry a great risk of affecting the patient’s well being and safety [14].

However, the described observations and putative advantages of the robotic technology are based solely on case series, case reports and experimental data, as high-quality clinical trials to demonstrate the benefits of the da Vinci Single-Site™ cholecystectomy have not been performed to date. The present study assesses in a randomized setting whether robot-assisted Single-Site™ cholecystectomy provides a significant benefit compared with single-incision laparoscopic cholecystectomy in terms of surgeon’s stress load as a primary endpoint.

## Methods/Design

### Study objectives

The study is designed as a single-blinded randomized clinical trial with an intention to treat analysis that compares Single-Site robot-assisted with single-incision laparoscopic cholecystectomy. It aims to to test the hypothesis that the robotic approach provides significant benefits in terms of a reduced surgeon’s stress load compared to the conventional single-incision approach, while matching its standards with regard to peri- and postoperative outcomes. The study directly compares both surgical approaches in patients with benign gallbladder disease.

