### Endpoints and data collection

The primary endpoint of the study is the surgeon’s physical and mental stress load at the time of surgery and is assessed by two validated visual analogue scales, specifically a modified Local Experienced Discomfort (LED, Fig. 1) and Subjective Mental Effort Questionnaire (SMEQ, Fig. 2) [7, 15]. Secondary endpoints include intra-operative blood loss, operating time, intra-operative conversion rate and additional trocar placement, complications, length of hospital stay, costs of procedure, Health-Related Quality of Life (HRQoL) and cosmesis. HRQoL and cosmesis will be assessed using the validated Gastrointestinal Quality of Life Index (GIQLI) and the Body Image Questionnaires (BIQ), respectively [16, 17]. The exact type and time of data collection is listed in detail in Table 1, the study flowchart is depicted in Fig. 3. All data will be recorded safely using the SecuTrial™ program. The estimated total duration of the study is 1.5 years, including the scheduled 1-month and 1-year postoperative follow-up visits. At the time of writing, the study is still active and the recruitment of patients has just been completed.

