### Power of the study

Sample-size calculations are based on the results of the previously mentioned experimental setup by Schatte et al. [7], utilizing an estimated effect size of 0.8, at a power of 0.8 and an alpha-error level of 0.05, as well as considering a potential additional error margin of 10–15% of the calculations (G-Power 3.1 software, Heinrich-Heine University Duesseldorf/Germany). The sample-size calculations resulted in a number of 30 randomized patients per arm (60 patients in total).

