### Statistical analysis

For descriptive statistics, median and mean with standard deviation will be used. For inductive statistics, the Chi-square and Fisher’s Test will be used to analyse contingency tables. In normally distributed data, a parametric two-sided Student’s T-Test (unpaired) to compare the data distributions in the two groups. In data that deviate from normal distribution, a two-tailed Mann–Whitney test will be applied to compare the data distributions in the two groups. All statistical analyses will be performed using SPSS (Version 22.0 and subsequent versions). P-values below 0.05 will be considered significant. No interim analyses are planned for the study.

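### The hypothesis claims that robotic surgery matches the conventional approach on peri- and postoperative outcomes, but the stated difference tests and sample size cannot support that claim

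*Protocol article*

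**What the plan says.** Under Study objectives, the protocol article says that the trial aims to "test the hypothesis that the robotic approach provides significant benefits in terms of a reduced surgeon’s stress load", and the same sentence adds "while matching its standards with regard to peri- and postoperative outcomes". The Methods paragraph of the abstract puts the same condition into the study question: "while matching the standards of the conventional single-incision approach with regard to peri- and postoperative outcomes".

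The outcomes concerned are secondary endpoints. Endpoints and data collection lists them: "Secondary endpoints include intra-operative blood loss, operating time, intra-operative conversion rate and additional trocar placement, complications, length of hospital stay", followed by costs, quality of life and cosmesis.

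For categorical data, Statistical analysis states that "the Chi-square and Fisher’s Test will be used to analyse contingency tables". For continuous data it names a two-sided unpaired t-test or a two-tailed Mann–Whitney test. The only decision criterion given is p below 0.05.

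Power of the study describes one calculation, "utilizing an estimated effect size of 0.8, at a power of 0.8 and an alpha-error level of 0.05", leading to 30 patients per arm. The abstract makes clear that this effect belongs to the primary endpoint: "utilizing an estimated effect size of surgeon’s comfort of 0.8".

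**The concern.** A test of difference can give evidence that two arms differ. It cannot, by failing to reach significance, give evidence that they are alike, because a small trial often fails to reach significance whatever the truth. So one limb of the stated hypothesis has no stated analysis that could answer it.

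The limb matters in practice. The primary benefit goes to the surgeon, and the Discussion hopes that the results will inform the choice of technique. Patients doing no worse is part of the case for adopting the robotic approach. If complications or conversions were described as matched because p was 0.05 or more, a material disadvantage could pass unremarked.

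**Working it through.** **Inputs from the article:** 30 per arm; effect size 0.8, power 0.8, alpha 0.05; an added allowance of 10–15%; two-sided tests. **Assumptions:** the article gives no event rates, SDs or margins for the secondary outcomes, so those below are illustrative and shown as a range.

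**1. The plan's own figure.** Per arm, n = 2(1.960 + 0.842)²/0.8² = 24.5, so 25. The exact noncentral t calculation gives 25.5, so 26. The allowance, stated as "considering a potential additional error margin of 10–15% of the calculations", gives 26/0.90 = 28.9 and 26/0.85 = 30.6 (29 to 31), or 26 × 1.10 = 28.6 and 26 × 1.15 = 29.9 (29 to 30). The stated 30 reproduces for the superiority comparison on stress load. With all 30 per arm analysed, power for 0.8 is about 86%.

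**2. A result that needs no assumed rates.** For complications in 0/30 versus 5/30, the two-sided Fisher p is 2 × C(30,5)/C(60,5) = 2 × 142,506/5,461,512 = 0.052. With no events in one arm, six in the other (20%) are needed for p<0.05. The choice of test matters here. The uncorrected chi-square is 60 × (5 × 30)²/(30 × 30 × 5 × 55) = 5.45, p = 0.020. The article names both tests, but the expected event count is 2.5 per arm, where Fisher's test is the usual choice.

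**3. Probability of a non-significant result, 30 per arm.** Exact Fisher power sums the binomial probabilities of all tables with p<0.05. The last column uses a normal approximation to the two-proportion test, which is less conservative.

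| Assumed true rates | Fisher power | Non-significant (Fisher) | Non-significant (normal approx.) |
|---|---|---|---|
| 5% vs 15% | 9.3% | 91% | 75% |
| 10% vs 20% | 9.6% | 90% | 81% |
| 5% vs 20% | 24% | 76% | 58% |
| 10% vs 30% | 37% | 63% | 51% |

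**4. Precision.**
- Binary outcome, 10% in both arms: 95% half-width = 1.96 × √(2 × 0.10 × 0.90/30) = 1.96 × 0.0775 = 0.152, about 15 points.
- No events in 30: exact upper 95% limit = 1 − 0.025^(1/30) = 11.6%.
- Continuous outcome: half-width = t(58; 0.975) × √(2/30) = 2.002 × 0.258 = 0.52 SD.

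**5. Which margins 30 per arm could exclude.** The calculation takes a true difference of zero and a one-sided 0.025 level. Power = Φ(margin/SE − 1.96), with SE = √(2/30) = 0.258 SD for continuous outcomes and √(2p(1−p)/30) for binary ones.

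| Outcome | Margin | Power at 30 per arm | Needed per arm for 80% |
|---|---|---|---|
| Continuous | 0.3 SD | 21% | 175 |
| Continuous | 0.5 SD | 49% | 63 |
| Continuous | 0.8 SD | 87% | 25 |
| Binary, 5% in both arms | 10 points | 43% | 75 |
| Binary, 5% in both arms | 15 points | 76% | 34 |
| Binary, 10% in both arms | 10 points | 25% | 142 |
| Binary, 10% in both arms | 15 points | 49% | 63 |

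The design can therefore rule out a disadvantage of about 0.8 SD, but is unlikely to rule out 0.5 SD or less, or 10 points at these rates.

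**The case against.** The strongest reply is that the clause is a passing remark about secondary endpoints. Stress load is the primary endpoint, the Background states the study question without any matching condition, secondary endpoints are ordinarily unpowered, and the article never uses the term non-inferiority. All of that is true, and it limits the weight of the point. It does not remove it, because both Study objectives and the abstract attach the clause to what the trial sets out to show.

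A reader might go further, in four ways that the documents do not support.

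- *That the plan will read p≥0.05 as equivalence.* No section says so. Statistical analysis defines only what counts as significant, and the Discussion draws no equivalence conclusion. What stands is that no other route to the claim is stated.
- *That a non-significant result is almost certain even when robotic surgery is clearly worse.* This fits a doubling from 10% to 20% under Fisher's test. It does not fit 10% versus 30%, where the probability is 63%, or about half under the less conservative approximation.
- *That the trial cannot show similarity at all.* This depends on the margin. Very wide margins are within reach.
- *That leaving out a margin or confidence intervals is itself an error.* A condensed article may leave these to the full protocol or analysis plan. The point rests on what the article does state: a hypothesis, a set of tests and a sample-size basis that do not fit together.

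**Conclusion.** The point holds as a mismatch within the article. The hypothesis and study question include a similarity claim, the stated inference consists of difference tests at p<0.05, and 30 per arm was derived for stress load alone. A difference test cannot support the matching limb, and the precision available (about ±15 points at a 10% event rate, ±0.52 SD for continuous outcomes) leaves room for material disadvantages.

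The binary figures rest on assumed event rates, and those in the last table on assumed margins as well. The 0/30 versus 5/30 result rests on neither, but does depend on using Fisher's test. The ±0.52 SD needs only 30 analysed per arm with a common SD.

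This should be corrected, but it does not threaten the trial's main result: the primary endpoint, its test and the sample size of 30 per arm are untouched.

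**What to change.** 1. Remove the matching clause from the hypothesis under Study objectives and from the study question in the abstract, or restate it as an aim to estimate the differences in the secondary outcomes.
2. Report each peri- and postoperative outcome as an arm difference with a 95% confidence interval, under the intention-to-treat analysis already specified. For sparse binary outcomes, use an interval suited to small counts.
3. State that a non-significant difference will not be reported as equivalence.
4. If matching is kept for any named outcome, conclude it only when the confidence interval excludes a margin fixed and justified before the analysis, and state the power that 30 per arm gives for that margin.

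The article reports that recruitment has just been completed, so enlarging the trial is not a practical route. The changes need no new patients or data, only wording and intervals. The price is a more modest conclusion on the patient outcomes.

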### Endpoints and data collection

The primary endpoint of the study is the surgeon’s physical and mental stress load at the time of surgery and is assessed by two validated visual analogue scales, specifically a modified Local Experienced Discomfort (LED, Fig. 1) and Subjective Mental Effort Questionnaire (SMEQ, Fig. 2) [7, 15]. Secondary endpoints include intra-operative blood loss, operating time, intra-operative conversion rate and additional trocar placement, complications, length of hospital stay, costs of procedure, Health-Related Quality of Life (HRQoL) and cosmesis. HRQoL and cosmesis will be assessed using the validated Gastrointestinal Quality of Life Index (GIQLI) and the Body Image Questionnaires (BIQ), respectively [16, 17]. The exact type and time of data collection is listed in detail in Table 1, the study flowchart is depicted in Fig. 3. All data will be recorded safely using the SecuTrial™ program. The estimated total duration of the study is 1.5 years, including the scheduled 1-month and 1-year postoperative follow-up visits. At the time of writing, the study is still active and the recruitment of patients has just been completed.

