**Fig. 2 Fig2:**
[figure not shown]
Subjective Mental Effort Questionnaire (SMEQ) visual analogue scale

**Table 1 Tab1:** Study outline

Schedule	Enrollment	Surgery	Inpatient assessment	1st Outpatient follow-up	2nd Outpatient follow-up^c^
Assessment No.	1	2	3	4	5
Time	–6 weeks to 0	0	up to 1 week^b^	1mo^b^	1 year
Informed consent	x				
Medical history	x				
In-/exclusion criteria	x				
Physical examination	x		x	x	(x) ^c^
Registration	x				
Imaging^a^	x				
Randomization	x				
Questionnaire 1: LED (surgeon)		x			
Questionnaire :2 SMEQ (surgeon)		x			
Duration of surgery		x			
Intraoperative blood loss		x			
Intraoperative conversion		x			
Evaluation of complications			x	x	x
Length of hospital stay			x		
Costs of procedure			x		
Questionnaire 3: HR-QoL (patient)	x			x	x
Questionnaire 4: Cosmesis (patient)				x	x

Each x signifies one test, report, or procedure

^a^USS and/or CT and/or MRI abdomen

^b^In case of AE, inpatient assessment and/or outpatient FU-visit might exceed the given time limit; All patients will be assessed until the day of discharge and 3–4 weeks after surgery

^c^The 2nd postoperative follow-up of the patient may either be done in the outpatient clinic or the assessement may be conducted by phone. In case the patient is seen in the outpatient clinic, the insurance company of the participant will not be charged by the hospital

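### The primary endpoint rests on two scales with no stated success rule, so the stated alpha of 0.05 (if either scale suffices) or power of 0.8 (if both are required) is not assured

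*Protocol article*

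**What the plan says.** Protocol article, Endpoints and data collection: "The primary endpoint of the study is the surgeon’s physical and mental stress load at the time of surgery", and it "is assessed by two validated visual analogue scales", namely a modified LED and the SMEQ. Table 1 lists LED and SMEQ as two separate questionnaires, both completed by the surgeon at the time of surgery.

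Statistical analysis gives a two-sided unpaired t-test, or a Mann–Whitney test for non-normal data, and one general threshold: "P-values below 0.05 will be considered significant". It gives no composite of the two scales, no order of testing, no requirement that both be significant and no division of alpha.

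Power of the study bases the sample size on a simulated experiment, "utilizing an estimated effect size of 0.8, at a power of 0.8 and an alpha-error level of 0.05", plus a margin of 10–15%, giving 30 per arm. It names no scale. The abstract describes the input as an "estimated effect size of surgeon’s comfort of 0.8", which is neither LED nor SMEQ.

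**The concern.** With two primary scales there are four possible outcomes, and the article settles only two of them: both significant and neither significant. If the robotic approach lowers LED but not SMEQ, or the reverse, the text supports calling the trial positive and equally supports calling it negative.

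The gap also affects the design figures. A single alpha and a single power describe a single test. With two tests, the rule that links them determines either the false-positive rate or the power. The Background section credits the source experiment with reductions in both cognitive and physical stress, so two effects were in view, yet one was used for sizing. The article also says that recruitment has just been completed. As the scales are filled in at surgery, most of the primary data probably exist already, so the rule needs to be on record soon.

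**Working it through.** **Inputs from the article:** standardised effect d = 0.8, alpha 0.05, power 0.8, margin 10–15%, 30 per arm (Power of the study); two-sided unpaired t-test and threshold 0.05 (Statistical analysis); two scales (Endpoints and data collection).

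**Assumptions, because the article gives no figure:** d = 0.8 on both scales; correlation between the scales within an arm from 0 to 0.9; operations treated as independent, as the planned t-test does.

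**1. Reproduce the stated sample size.** Power at n per arm is P(|T| > t(1 − α/2; 2n − 2)), where T is noncentral t with noncentrality d·√(n/2).
- n = 25: power 0.791.
- n = 26: noncentrality 0.8 × √13 = 2.88, power 0.807. So 26 per arm are needed.
- Margin: 26 × 1.10 = 28.6 and 26 × 1.15 = 29.9, or 26/0.90 = 28.9 and 26/0.85 = 30.6. This gives 29 to 31, which agrees with the stated 30.
- n = 30: noncentrality 0.8 × √15 = 3.10, power 0.861 for one scale at 0.05.

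The stated figure is therefore a calculation for one outcome at the full alpha.

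**2. Success if either scale has p < 0.05.** At correlation 0 the false-positive rate is 1 − 0.95² = 0.0975. Other correlations use the bivariate normal distribution.

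**3. Success only if both scales have p < 0.05.** The error rate stays at or below 0.05. At correlation 0, joint power is 0.861² = 0.74 at 30 per arm and 0.807² = 0.65 at 26.

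**4. Holm at an overall 0.05.** The smaller p-value must be below 0.025; if it is, the other is tested at 0.05. One-scale power at 0.025 is q = 0.785 (n = 30) and 0.716 (n = 26). At correlation 0:
- Error rate if neither scale differs: 1 − 0.975² = 0.049.
- Power for at least one scale, n = 30: 1 − (1 − 0.785)² = 0.95.
- Power for a given scale, q + (p − q)·q, where p is one-scale power at 0.05: n = 30, 0.785 + (0.861 − 0.785) × 0.785 = 0.845; n = 26, 0.716 + (0.807 − 0.716) × 0.716 = 0.78.

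Results over the range, from the bivariate normal approximation and simulation with 100,000 runs:

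| Correlation | Either at 0.05: false positives | Both at 0.05: power, n = 30 | Both at 0.05: power, n = 26 | Holm, at least one, n = 30 | Holm, per scale, n = 30 | Holm, per scale, n = 26 |
|---|---|---|---|---|---|---|
| 0 | 9.75% | 0.74 | 0.65 | 0.95 | 0.85 | 0.78 |
| 0.5 | 9.1% | 0.77 | 0.70 | 0.90 | 0.84 | 0.77 |
| 0.8 | 7.8% | 0.81 | 0.74 | 0.86 | 0.82 | 0.76 |
| 0.9 | 7.0% | 0.82 | 0.76 | 0.84 | 0.82 | 0.76 |

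**The case against.** Several counter-arguments carry weight.

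- **One hypothesis.** The article states one hypothesis and one endpoint, physical and mental stress load. Read as a conjunction, alpha is controlled and only power is in question. That reading is possible, but the text does not adopt it. Equally, the idea that each scale alone supports a primary claim at 0.05 is inferred from the general threshold; the article does not say so.
- **Unseen documents.** A full protocol or analysis plan could hold the missing rule. It therefore cannot be said that the success criterion was left to be chosen after the results. Such a rule would settle alpha, but the published power would still be a figure for one unnamed outcome.
- **Few losses.** Both scales are completed at surgery, and the 10–15% is described as a margin of the calculations, not as dropout. The figures at 30 per arm are therefore the more relevant, and those at 26 are a lower bound.

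A reader might go further and infer that alpha 0.05 and power 0.8 cannot both hold. The numbers contradict this. Holm keeps the error at 0.05 and exceeds 0.8 power per scale at 30 per arm, and a both-required rule reaches 0.80 at a correlation of about 0.75 to 0.8. A reader might also quote 0.785 and 0.716 as the per-scale power under Holm. Those figures belong to a flat 0.025 per scale and understate Holm. Nor can a multiplicity figure be attached to the secondary endpoints, because the article does not give the number of comparisons.

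**Conclusion.** The point holds as a gap between the primary endpoint and the stated design figures. Two separately recorded scales share one threshold and one effect size, and nothing in the article says which result counts as success. What follows depends on the missing rule: about 7–10% false positives instead of 5% if either scale suffices, or joint power of about 0.74–0.82 at 30 per arm (0.65–0.76 at 26) instead of 0.8 if both are required.

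The power ranges rest on d = 0.8 for both scales, which the article does not claim for either by name, and both sets of ranges rest on an assumed correlation of 0 to 0.9. A smaller effect on one scale would lower the joint power further. The sample size itself is correctly computed for one outcome and need not be called wrong.

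**What to change.** Before the primary results are examined, record one rule and the power that belongs to it.

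- **Recommended:** test LED and SMEQ by Holm at an overall two-sided 0.05, and make a separate claim for each scale that passes. State the power at d = 0.8 on both scales: at 30 per arm about 0.82–0.85 per scale and 0.84–0.95 for at least one; at 26 per arm about 0.76–0.78 per scale.
- **If the intended claim is physical and mental stress together:** require both at 0.05 and restate joint power as about 0.74–0.82 at 30 per arm.

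The choice must be made in advance because the rules can disagree. Two p-values between 0.025 and 0.05 succeed under the second rule and fail under Holm. In either case, say which scale the effect size of 0.8 was taken from.

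The cost is a paragraph of text. Under Holm the first scale faces a stricter threshold (0.025); under the joint rule the stated power may fall below 0.8. No new patients or data are needed.
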